# Impact of a procalcitonin-based algorithm on the quality of management of patients with uncomplicated adhesion-related small bowel obstruction assessed by a textbook outcome: a multicenter cluster-randomized open-label controlled trial

**DOI:** 10.1186/s12876-022-02144-w

**Published:** 2022-03-02

**Keywords:** Procalcitonin, Small bowel, Obstruction

## Abstract

**Background:**

Acute adhesion-related small bowel obstruction (ASBO) is a common digestive emergency, accounting for 1 to 3% of all digestive emergencies. The efficacy of conservative management in this setting is a subject of debate, as it may delay the decision to perform surgery and increase the frequency of bowel resection (e.g., in the presence of bowel necrosis) or, in contrast, prompt an excessive number of unnecessary laparotomies. Thus, the decision to perform surgery is difficult. We propose that the introduction of the procalcitonin (PCT)-based algorithm improves the quality of the management of patients with ASBO by aiding the decision of whether or not to perform surgery.

**Methods:**

This is a 1:1 cluster-randomized clinical trial (use of algorithm: no algorithm) using an independent computer to ensure that investigators cannot interfere with the randomization. Each cluster will correspond to one investigating center. All patients in a center will be managed in the same way. Before randomization, each principal investigator will provide a commitment to participate in the study to avoid the risk of “empty clusters”. The patients included will constitute two parallel arms (use of algorithm versus no algorithm), with no expected crossover between arms. The inclusion criteria are being an adult with uncomplicated acute ASBO (i.e., absence of fever, abdominal pain and distension, nausea and/or vomiting, and the absence of gas and/or stool, in conjunction with a contrast-enhanced CT scan, for patients with previous abdominal surgery) who is able to express consent with a signed written informed consent form. Patients with complicated acute ASBO (strangulation or peritonitis) will be excluded.

**Discussion:**

There is an ongoing debate on the management of uncomplicated ASBO. The main points are to avoid a surgery if it is unnecessary and to avoid delayed surgery if it is necessary. Currently, there are no robust criteria to objectively determine the failure of non-surgical treatment or to establish the indications for surgery in acute ASBO. Our team proposes the use of procalcitonin (PCT) to help distinguish patients for whom conservative management is likely to be successful from those for whom surgical management is required. The results from a randomized control trial could help in the selection of patients through clear inclusion and exclusion criteria and simplify or clarify the management algorithm. In conclusion, PCT may be useful in evaluating the proper strategy for ASBO.

*Trial registration* The trial is registered at clinical trials under the reference: NCT03905239

## Background

Acute adhesion-related small bowel obstruction (ASBO) is a common digestive emergency, accounting for 1 to 3% of all digestive emergencies [1, 2]. It is associated with a mortality rate of between 2 and 8%, although this figure may be as high as 25% when surgical treatment is delayed [3–6]. According to a study based on the medical records of the Scottish National Health Service over a 10-year period, 5.5% (n = 1169) of the 21,347 patients admitted for ASBO underwent surgery [7]. The associated costs are non-negligible (approximately $9000 for cases with conservative management and between $30,000 and $40,000 for cases requiring surgery) [8]. In 2013, the working group on ASBO of the World Society of Emergency Surgery suggested two distinct approaches for the management of acute ASBO [9]. Conservative (i.e., non-surgical) management can be initiated when there are “no signs of strangulation or peritonitis or a history of persistent vomiting or combination of CT scan signs (free fluid, mesenteric edema, small bowel feces signs, devascularized bowel)”, whereas surgical management (with or without bowel resection) must be initiated before or during conservative management in the event of “free intraperitoneal fluid, mesenteric edema, the presence of small bowel feces signs by CT, a history of vomiting, severe abdominal pain (VAS > 4), abdominal guarding, elevated WCC, and devascularized bowel by CT” [9]. Conservative management includes the use of a nasogastric tube (NGT), intravenous administration of fluids, and clinical and biochemical monitoring for 24 to 72 h [9]. However, the efficacy of conservative management in this setting is a subject of debate, as it may delay the decision to perform surgery and increase the frequency of bowel resection (e.g., in the presence of bowel necrosis) or, in contrast, prompt an excessive number of unnecessary laparotomies. Surgical management consists of adhesiolysis and (in some cases) bowel resection.

Currently, there are no robust criteria to objectively determine the failure of non-surgical treatment or establish the indications for surgery in acute ASBO. Gastrografin has been evaluated in this setting but several meta-analyses failed to show any benefit of gastrografin [10].

As no criterion can be used to identify the failure of conservative management or propose surgery as initial management, biomarkers, such as procalcitonin (PCT), have been investigated in this setting. PCT has been described as a marker of infection and inflammation. We previously tested PCT as a discriminant factor for necrosis in mesenteric infarction, with a cutoff of 2.4 ng/ml [11]. Then, our team proposed the use of PCT to help distinguish patients for whom conservative management is likely to be successful from those for whom surgical management is required. Cutoffs of 0.2 µg/L (for failure of conservative management) and 0.6 µg/L (for need for surgery) accurately identified more than 80% of patients [12]. These cutoffs and data were confirmed in a second independent cohort and were then used to propose an algorithm for the management of patients with ASBO. In this single-center, retrospective, case–control study, we showed that the introduction of this algorithm to patient management reduced i/ the time to surgery, with no increase in the surgical management rate, and ii/ the length of stay (with a 2-day difference) [13].

We propose that introduction of the PCT-based algorithm will improve the quality of management of patients with ASBO. We expect that the arm combining standard management with the PCT-based algorithm will be superior to the arm with standard management alone in terms of the success rate for patients with ASBO. If the algorithm is shown to improve patient management and is cost-effective, it could be proposed in routine clinical practice.

## Methods/design

### The aim, design, and setting of the study

#### The aim

The primary objective of the study is to assess the impact of a PCT-based algorithm on the textbook outcome at postoperative day 90. The secondary objectives are to compare short-term and long-term recurrence rates, quantify and compare patient satisfaction, compare morbidity according to the type of management, compare the length of stay, propose other markers of ischemia (copeptin, proadrenomedullin) to reinforce the value of PCT in the early stages of ASBO, and perform a cost-effectiveness analysis.

#### The design

This is a 1:1 cluster-randomized clinical trial (use of algorithm: no algorithm) using an independent computer to ensure that investigators cannot interfere with the randomization. Each cluster corresponds to one investigating center. Randomization is center-based, i.e., all patients will be managed in the same way. Before randomization, each principal investigator will provide a commitment to participate in the study to avoid the risk of “empty clusters”. Randomization will be performed using computer-generated random numbers by the trial methodologist before patient recruitment.

#### Setting

The trial will be open in 16 centers. Each of the 16 centers will be assigned to one arm (with or without the PCT algorithm) to avoid contamination between the two arms.

### Characteristics of the participants

Patients are eligible for inclusion if they are over 18 years of age, have an acute ASBO (abdominal pain and distension, nausea and/or vomiting, the absence of gas and/or stool, in conjunction with contrast-enhanced CT scan showing no other cause for obstruction for patients with previous abdominal surgery), without signs of complications (strangulation, peritonitis), are able to express consent, signed the written consent form, and are covered by national health insurance. They are not eligible for inclusion if they have had no previous abdominal surgery, if they have signs of strangulation, bowel ischemia or strangulation, if they have an obstruction within four weeks following a previous surgery, an ongoing or history of bowel cancer, an ongoing or history of inflammatory bowel disease, a history of abdominal radiotherapy, an active infection, or a contraindication to contrast-enhanced CT.

The target population is defined as patients requiring management for CT-scan-confirmed uncomplicated adhesion-related small bowel obstruction. These patients will be recruited by public hospital emergency department consultations (university and non-university hospitals).

### Processes, interventions, and comparisons

In the algorithm group, patient management will be based on clinical examination and PCT assessment. PCT will be assayed on admission. If PCT is between 0.2 and 0.6 µg/L, a second assay will be performed 24 h after admission (Fig. 1). From 48 h after the initiation of conservative management or in the absence of bowel function, operative management (adhesiolysis or bowel resection) will be performed. In the event of discordance between PCT values and the clinical examination i.e., the presence of persistent ASBO or signs of complications, management will be based on the clinical examination. Conservative management will be continued for 48 h in the absence of signs of bowel ischemia and the presence of bowel function.

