**Fig. 1 Fig1:**
[figure not shown]
Synopsis of the study

In the control group, patient management will be based on clinical examination. Gastrografin will not be used in the control arm, as data from a recent randomized clinical trial that included 242 patients (ABOD study [10]), combined with the results of a meta-analysis performed in 2015 that included 990 patients, failed to demonstrate the value of gastrografin to reduce the surgery rate and length of stay. Gastrografin may therefore no longer be indicated in this setting. The use of gastrografin could also introduce a bias in the interpretation of the outcome, as the outcomes could be considered to be related to gastrografin and not exclusively to the algorithm. Conservative management will be continued for 48 h in the absence of signs of bowel ischemia and the presence of bowel function.

From 48 h after the initiation of conservative management or in absence of bowel function, operative management (adhesiolysis or bowel resection) will be performed.

There is no blinding procedure, as blinding is not possible/necessary because each center will be randomized to one study arm and all patients in each center will be managed according to the same strategy.

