### Outcomes

The primary endpoint will be the proportion of patients achieving the textbook outcome, defined as patients either appropriately undergoing surgery (ischemia confirmed at operation ± resection) or appropriately managed conservatively (no need for surgery) with no major postoperative complications (Clavien–Dindo ≥ 3) and a medical length of stay < 5 days (defined as the time at which the patient is medically eligible for discharge), with no postoperative consultation, rehospitalization, or reoperation within 90 days after randomization. The textbook outcome is defined as that proposed by Kolfschoten [14] for colon cancer resection. The primary endpoint will be analyzed by an open-label design. The centers will record all cases of (i) no readmission, (ii) no unplanned consultation for nausea, vomiting, and/or the absence of gas and/or stool, (iii) no hospitalization, (iv) no reoperation, and (v) no recurrence that could occur after the patient’s discharge and before the two visits scheduled in the protocol (1 and 3 months). If the quality of the completion of the primary endpoint is not sufficient after monitoring of the first-recruited patients, the adjudication committee will be contacted.

The secondary endpoints are the 1-, 3-, 6-, 9-, 12-month recurrence rates, defined as a new episode of adhesion-related small bowel obstruction, the EVAN G score to evaluate patient satisfaction at postoperative month 1 [15], the Clavien and CCI scores to assess morbidity evaluated after the patient’s discharge at postoperative month 1, the hospital length of stay, defined as the interval between admission to the emergency department and discharge from the ward, and the cumulative length of stay, defined as the total number of days of hospitalization related to ASBO at postoperative month 12.

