## Discussion

The management of complicated ASBO is straightforward, as surgery is required. There is, however, an ongoing debate concerning the surgical management of uncomplicated ASBO [16]. The main points are to avoid surgery if it is unnecessary and to avoid delaying surgery if it is necessary. A recent propensity score analysis of 27,904 patients showed a lower risk of recurrence than with conservative management (13.0% vs 21.3%, p < 0.01). Another study of 6,191 patients confirmed these outcomes (19% vs 25.6%, p < 0.005). However the authors noted a higher mortality rate in the operative group (3.7% vs 2.6%, p = 0.025) [17]. The debate is still ongoing and conservative treatment remains the standard of care whenever possible.

Currently, there are no robust criteria for objectively determining the failure of non-surgical treatment or establishing the indications for surgery in acute ASBO. Soluble contrast medium (such as gastrografin) is still used in a number of centers as a diagnostic test for the resolution of small bowel obstruction when it is observed in the cecum by abdominal X-ray. The therapeutic effect of water-soluble contrast medium is due to a side effect based on the stimulation of bowel peristalsis [10]. However, the efficacy of water-soluble contrast medium in this setting is also subject to debate, as data from a recent randomized clinical trial that included 242 patients (ABOD study), combined with a meta-analysis in 2015 that included 990 patients, failed to demonstrate any value of gastrografin to reduce the surgery rate and length of stay [11, 12]. In the ABOD study, the operative intervention rate was 24% in the gastrografin arm and 20% in the control arm (p = NS) and the bowel resection rate was 8% in the gastrografin arm and 4% in the control arm (p = NS). These results, combined with those of a meta-analysis based on 10 published studies, suggest that gastrografin did not decrease either the operative intervention rate (26% in the gastrografin arm versus 21% in the control arm) or the number of days from initial CT to discharge (3.5 versus 3.5, p = NS for both) [12].

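### In both arms the written trigger for surgery joins 48 h and absent bowel function with 'or', so followed literally it mandates operations that the primary endpoint counts as failures

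*Protocol article*

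**What the plan says.** All references are to the protocol article.

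- **Algorithm arm** (Processes, interventions, and comparisons): "From 48 h after the initiation of conservative management or in the absence of bowel function, operative management" is to be carried out. Procalcitonin (PCT) is measured on admission and repeated at 24 h if it lies between 0.2 and 0.6 µg/L. Where PCT and the clinical findings disagree, i.e. "the presence of persistent ASBO or signs of complications, management will be based on the clinical examination".
- **Control arm** (same section, after the Fig. 1 caption): management rests on clinical examination. The same trigger then follows: from 48 h "or in absence of bowel function, operative management (adhesiolysis or bowel resection) will be performed".
- **Both arms**: conservative treatment goes on for 48 h "in the absence of signs of bowel ischemia and the presence of bowel function".
- **Eligibility** (Characteristics of the participants): the presenting picture includes "the absence of gas and/or stool, in conjunction with contrast-enhanced CT scan".
- **Primary endpoint** (Outcomes): success means "patients either appropriately undergoing surgery (ischemia confirmed at operation", with or without resection) or "appropriately managed conservatively (no need for surgery) with no major postoperative complications", together with fitness for discharge in under 5 days and no return to care within 90 days.

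**The concern.** The trigger is mandatory, and either limb is enough to set it off. Neither limb alone describes a failed trial of conservative treatment: one is a time without a clinical condition, the other a clinical condition without a time. The companion sentence does not repair this. It makes the 48-h conservative course depend on bowel function being present, which fits the literal reading of the trigger.

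These sentences set the operating rule in both arms. In the control arm they are the only stated rule beyond clinical examination, so they define the comparator. An operation that the rule requires but that finds no ischemia is a primary endpoint failure. The treatment rule, taken at its word, therefore works against the outcome by which the trial is judged.

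**Working it through.** No figure in the plan is at stake, so there is nothing to reproduce numerically. The check sets the trigger, the continuation condition, eligibility and the endpoint side by side and follows each kind of patient through them.

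**Inputs**
- Trigger: (T1) 48 h since the start of conservative treatment, OR (T2) bowel function absent.
- Continuation to 48 h: no signs of ischemia AND bowel function present.
- Eligibility: gas and/or stool absent.
- Endpoint: surgery succeeds only with ischemia found; conservative care succeeds if no surgery was needed and the patient is medically fit for discharge in under 5 days. The other endpoint conditions are assumed met throughout.
- Assumption: bowel function means passing gas or stool. The article does not define it.

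**Intended rule, as far as it can be inferred**: surgery if function has not returned by 48 h, or earlier for signs of ischemia or other complications.

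| Patient (no ischemia in A to D) | Literal rule | Endpoint if followed | Inferred intent |
|---|---|---|---|
| A. Neither gas nor stool at entry | T2 true at hour 0; continuation condition false; surgery | Failure | Conservative care up to 48 h |
| B. Function back, still under conservative care at 48 h, recovering | T1 true; surgery | Failure | Continue; success if fit for discharge in under 5 days |
| C. Recovered and conservative care ended before 48 h, function present throughout | Neither limb met | Success | Same |
| D. Function present earlier but lost, still absent at 48 h | Surgery, by T2 when lost or by T1 at 48 h | Failure | Surgery at 48 h; also failure |
| E. Signs of ischemia | Continuation condition false; surgery | Success if ischemia confirmed | Same |

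**What follows**
1. Rows A and B are where the literal rule departs from any sensible reading. A turns on T2 having no time attached, B on T1 having no failure condition.
2. In row A within the algorithm arm, a patient with PCT between 0.2 and 0.6 µg/L would be due for surgery at entry, so the 24-h assay would come too late to guide the decision.
3. Because eligibility says and/or, a patient may be enrolled with only one of gas and stool absent. Whether T2 is met for that patient depends on the missing definition. Row A is therefore limited to those with neither.
4. Row C shows that the conflict with the endpoint is partial. Conservative success remains open to patients who recover before 48 h.
5. Row D fails the endpoint under both readings. That follows from how the endpoint defines appropriate surgery, and rewording the trigger does not change it.

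**Size**: the shares of patients in rows A and B are not given, so no effect on the success rate can be computed.

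**The case against.** **The governing chart cannot be seen.** The algorithm text points to Fig. 1, the Discussion says each center follows one uniform chart, and the article condenses a fuller protocol. Centers may be working from a correct chart. This stands, and it limits what can be said about conduct. It does not make the printed sentences right, and they should agree with the chart.

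**Context excludes the literal reading.** Both arms provide for 48 h of conservative care and the algorithm arm schedules a 24-h assay, which would be pointless for many patients if absent gas or stool at entry meant immediate surgery. That is good evidence of intent. But the 48-h provision is itself conditional on bowel function being present, so it does not rescue row A.

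**Clinical examination governs.** Both arms open by basing management on it, and few surgeons would operate on a patient who has recovered. That is likely true in practice. Still, the trigger is worded as an instruction. The discordance rule settles conflicts between PCT and the clinical findings, exists only in the algorithm arm, and does not amend the trigger.

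**Stronger readings a reader might infer, and why they are not supported**
- *Bias between arms.* The wording is essentially identical in both, and nothing shows that it would act differently in one.
- *Inflated between-center variation.* Centers could read the rule differently, but the document does not show that they rely on these sentences rather than the chart. The sample size already allows for clustering with an intra-class correlation of 0.015.
- *A measurable effect from the gap between 48 h and 5 days.* The difference is 120 − 48 = 72 h, but this is a span of hours, not a share of patients, and it assumes that both clocks start together.
- *Contradiction with the statement that* "conservative treatment remains the standard of care whenever possible". That is Discussion background on the surgical debate, not a trial rule.

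**Conclusion.** The point holds: the operating rule is wrong as written in both arms. The 48-h limb has no failure condition, and the bowel-function limb has no time. Followed literally, either can require surgery without ischemia, which the primary endpoint scores as failure.

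The 48-h part rests on the text alone. The at-entry part also rests on reading bowel function as passage of gas or stool, and applies to patients enrolled with neither. The conflict with the endpoint is partial, its effect cannot be sized from the document, and no bias between arms is claimed. Fig. 1 or the full protocol may already carry the correct rule. In that case the defect is confined to the article's text, which still needs correcting.

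**What to change.** In both arms, replace the trigger with wording such as: *Operative management will be performed if bowel function has not returned by 48 h after the start of conservative management, or earlier if signs of ischemia, strangulation or peritonitis appear.*

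Then:
- bring the sentence on continuing conservative care for 48 h into line, so that it no longer excludes patients whose function has yet to return;
- state what bowel function means;
- keep the PCT-based indications in the algorithm arm;
- make the text agree with Fig. 1 and the full protocol.

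The exact clinical wording belongs to the investigators, who should confirm it. The cost is a wording amendment and a memo to the 16 centers; no new data are needed.
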